### Economic evaluation

The economics will be evaluated in parallel to the trial, which is compatible with the design presented earlier. The purpose of this evaluation is to determine the potential efficiency of the SCPD in the ambulatory mental healthcare setting versus usual care for the caregivers, from a societal perspective. The economic evaluation will be based on the general principles of a cost-effectiveness analysis, and the outcome measures will be costs, time to institutionalization of the patient, and the quality-adjusted life years (QALYs). These outcome measures will be combined in two incremental cost-effectiveness ratios (ICERs): cost per QALY gained and cost per unit of time-to-institutionalization gained. We will build up an empirical estimate of the sampling distributions of both ICERs by resampling with replacement from the original data (i.e., bootstrapping). A cost-effectiveness acceptability curve will summarize the evidence in support of SCPD being cost-effective for all potential values of the willingness to pay for a QALY, or a unit of time-to-institutionalization. We will explore the impact of uncertainty surrounding deterministic parameters (such as cost prices) on the ICER by means of one-way sensitivity analyses on the range of extremes.

The cost analysis will consist of two main parts. In the first part, on the patient-caregiver dyad level, we will measure volumes of care prospectively, using the RUD questionnaire [42,64]. This instrument contains questions about the use of community care services, type of accommodation, the employment status of the person with a cognitive disorder and the primary informal caregiver, medical care, and informal care. Informal care-giving time will be categorized as a loss of production (friction-cost method) for an employed primary caregiver, and as a loss of leisure time in all other cases. The RUD instrument will be completed by the informal caregiver every 3 months from baseline to follow-up at 12 months. The time to institutionalization is the final event. In both treatment groups, SCPD and usual care, the patients who are still not institutionalized at the end of 12 months are considered as censored observations. The second part of the cost analysis consists of determining the cost prices for each volume of consumption in order to be able to multiply the volumes registered for each participating caregiver and each patient. The Dutch guidelines for cost analyses will be used [65]. If no guideline or standard prices are available for units of care/resources, we will determine real cost prices with the activity-based costing method [66,67].

The effect analysis will adhere to the design of a cluster, randomized, controlled trial. The relevant variables for the economic evaluation are the time to institutionalization and the quality of the caregiver's life. We will use QALYs computed with the trapezium rule for a cost-utility analysis of the two treatment groups. The time to institutionalization will be the final event, meaning that the quality of the caregiver's life will be researched until the time of the patient's institutionalization, with a maximum of 12 months. We will use the standard EQ-5D [43,44] classification system developed by the EuroQol Group for the overall quantification of health status as a single index (utilities). The EQ-5D is one of three widely used multi-attribute systems available to determine health state preferences (utilities). The arguments for choosing the EQ-5D are:

1. The five domains of the EQ-5D reflect aspects that are thought to be important for the population under consideration.

2. The system is relatively simple to administer.

3. The sensitivity of the instrument has proven satisfactory.

4. A reasonably sound algorithm has been published to compute utilities.

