**Informal caregivers**										
Sense of competence		✓			SCQ	✓				✓
Quality of life		✓			EQ-5D	✓				✓
Depressive symptoms		✓			CES-D	✓				✓
Caregiver distress		✓			NPI-Q	✓				✓
Time spent giving care			✓		RUD	✓	✓	✓	✓	✓
Age				✓	RUD	✓				
Gender				✓	RUD	✓				
Ethnicity				✓	RUD	✓				
Education				✓	RUD	✓				
Marital status				✓	RUD	✓				✓
Living arrangement				✓	RUD	✓				✓
Relation with the patient				✓	SCPD questionnaire	✓				
Shared household with the patient				✓	SCPD questionnaire	✓				✓

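### The informal-care costing rule sorts hours by whether the caregiver has a job, not by whether paid work was missed, so the incremental cost in both ICERs can be biased by an amount and in a direction the document does not determine

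*Protocol article*

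**What the plan says.** All of this is in the protocol article.

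- **Classification (Economic evaluation).** "Informal care-giving time will be categorized as a loss of production (friction-cost method) for an employed primary caregiver, and as a loss of leisure time", the latter "as a loss of leisure time in all other cases". The line is drawn by employment, and the residual category takes everyone else.
- **Volumes (Economic evaluation; Table 1).** The RUD is said to cover, among other topics, "the employment status of the person with a cognitive disorder and the primary informal caregiver, medical care, and informal care". For this volume Table 1 lists only "Time spent giving care", collected at baseline and every three months to month 12. No volume of missed working hours is named.
- **Costing step (Economic evaluation).** Prices are set in a second part of the cost analysis, where the Dutch costing guidelines are cited, and are then used to "multiply the volumes registered for each participating caregiver and each patient".
- **Use of the result (Economic evaluation).** The analysis is done "from a societal perspective", and costs feed "two incremental cost-effectiveness ratios (ICERs): cost per QALY gained and cost per unit of time-to-institutionalization gained". One-way sensitivity analyses are planned on deterministic parameters, with cost prices as the example.

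**The concern.** Production is lost when paid work is not done. A caregiver with a job also gives care outside working hours, and those hours displace leisure or unpaid time. The sentence gives an employed caregiver no such category. Followed literally, a full-time worker who gives 10 hours of care a week and misses no work is charged 10 hours of lost production. A caregiver with an 8-hour weekly job who gives 30 hours of care is charged more lost work than the job contains.

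The friction-cost method also counts production loss only up to a limit. If that limit is applied to all of an employed caregiver's care time, later hours receive no value at all, because the leisure category is closed to that caregiver.

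The trial's hypothesis is that patients in the SCPD arm stay at home longer. Caregiving time is one of the quantities most likely to differ between arms, and its price goes straight into the numerator of both ICERs and into the acceptability curves.

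**Working it through.** **Plan's own figure.** None exists for this rule, so there is nothing to reproduce. The only document input used below is the 28% v 14% institutionalized (Power calculations). Prices, hours, employed share and friction period are assumptions.

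**Step 1: form of the error.** Let s be the share of caregivers employed, w the share of their care hours that displaces paid work (taken as equal in both arms), dH the difference between arms (SCPD minus control) in their care hours, and Pprod and Pleis the two hourly prices. If every hour is priced as production with no friction limit, the error in incremental cost per dyad is

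s × (1 − w) × dH × (Pprod − Pleis).

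It is zero only if no caregiver is employed, all their care displaces work, their hours do not differ between arms, or the prices are equal.

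**Step 2: range under assumptions** (s 0.2 to 0.5, w 0.05 to 0.25, price gap 10 to 30 per hour).

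- dH = 50, low end: 0.2 × 0.75 × 50 × 10 = 75.
- dH = 150, high end: 0.5 × 0.95 × 150 × 30 = 2,137.5, about 2,140.
- dH = −50: from −(0.2 × 0.75 × 50 × 10) = −75 to −(0.5 × 0.95 × 50 × 30) = −712.5.

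**Step 3: time at home implied by the plan.** With constant hazards and deaths ignored, the yearly hazards are −ln(0.72) = 0.3285 and −ln(0.86) = 0.1508. Mean time at home within 12 months (52.18 weeks) is (0.28/0.3285) × 52.18 = 44.48 weeks for control and (0.14/0.1508) × 52.18 = 48.44 weeks for the SCPD. The gain is 3.96 weeks, of which 0.753 falls in the first five months.

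**Step 4: one employed caregiver** (assumed 20 h care and 4 h work missed per week in both arms; 30 euro/h production, 10 to 15 euro/h leisure).

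- Weekly cost as written: 20 × 30 = 600.
- Weekly cost split by work missed: 4 × 30 + 16 × 10 = 280, or 4 × 30 + 16 × 15 = 360.
- Over 3.96 weeks: 2,376 as written against 1,109 to 1,426 split, an excess of 950 to 1,267.
- Averaged over all dyads with s from 0.2 to 0.5: 0.2 × 950 = 190 to 0.5 × 1,267 = about 634.

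**Step 5: the same caregiver with a friction limit** (assumed five months from inclusion, applied to production loss under both rules).

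- As written: 600 × 0.753 = 452.
- Split: 120 × 0.753 + 160 × 3.96 = 724, or 120 × 0.753 + 240 × 3.96 = 1,041.

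The rule as written is now too low by 272 to 589, so the sign has reversed.

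**Step 6: how little removes or reverses the hours difference.** If weekly hours are lower in the SCPD arm, dH is zero when the ratio of weekly hours is 44.48/48.44 = 0.918. A reduction of about 8%, or 1.6 of 20 hours a week, cancels the effect of longer time at home. A larger reduction makes dH negative.

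**The case against.** **A charitable reading exists.** The grammatical subject is caregiving time, so the residual category could mean all other time, including an employed caregiver's hours that cost no work. Naming the friction-cost method points the same way, since an hour with no work missed has no friction cost. This has some force: the authors may have intended the correct split. But the sentence contrasts caregivers rather than hours, and two analysts could program different costs from it. The repair is the same under either reading.

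**The detail may sit elsewhere.** An article condenses, and the RUD and the Dutch guidelines may supply the split. The article lists RUD topics, not items, so it cannot be concluded that missed hours were not recorded. But the point is a stated rule, not an absent one, and the guidelines are cited for the later pricing step, not for the classification.

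**The planned sensitivity analysis may cover it.** If the price for employed caregivers' hours were lowered to the leisure price, the effect would be bounded. The plan does not name that scenario, and varying a price does not by itself reclassify hours.

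**The stronger reading fails.** A reader might infer that both ICERs are wrong, or that the rule makes the SCPD look too expensive because it adds caregiving hours. The document supports neither. It never says informal-care hours will be higher in the SCPD arm. The description of the SCPD allows professionals to arrange respite such as home or day care, which could lower weekly hours. Steps 5 and 6 show that a friction limit or a modest reduction in hours can cancel or reverse the sign.

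**Conclusion.** The concern holds as a fault in the wording of the costing rule. As written, the rule prices employed caregivers' non-work caregiving hours as lost production. The incremental cost shared by both ICERs is therefore biased unless those hours are equal between arms or the two hourly prices are equal.

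Size and direction cannot be derived from the document. The figures above, including 75 to 2,140 per dyad, are illustrations under assumed prices, hours, employed share and, in Step 5, friction period. They show that the error need not be negligible and need not favour either arm. The institutionalization outcome itself is not affected.

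The change is worth making before costs are analysed, because it is cheap and removes an ambiguity that reaches the main economic result.

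**What to change.** Replace the classification sentence with a rule to this effect: for employed primary caregivers, only paid working hours missed because of caregiving are valued as production loss by the friction-cost method; all their remaining caregiving hours, and all caregiving hours of caregivers without paid work, are valued as lost leisure time; no hour is counted twice.

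Name the data item from which missed hours are taken. If missed hours were not recorded, report both ICERs under two classifications as a named sensitivity analysis: all employed caregivers' hours at the leisure price, and all at the production price. State that true work absence cannot then be separated from other care time. An all-leisure base case alone would be debatable, since it drops real work absence from a societal analysis.

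Cost: one sentence, a small change in cost programming and one extra scenario. No further participants are needed.

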**Methods and design:**

In our ongoing, cluster, randomized, single-blind, controlled trial, the participants in six mental health services in four regions of the Netherlands have been randomized per service. Professionals of the ambulatory mental health services (psychologists and social psychiatric nurses) have been randomly allocated to either the intervention group or the control group. The study population consists of community-dwelling people with dementia and their informal caregivers (patient-caregiver dyads) coming into the health service. The dyads have been clustered to the professionals. The primary outcome measure is the patient's admission to a nursing home or home for the elderly at 12 months of follow-up. This measure is the most important variable for estimating cost differences between the intervention group and the control group. The secondary outcome measure is the quality of the patient's and caregiver's lives.

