### Ethical principles

The Committee on Research Involving Human Subjects, Arnhem-Nijmegen Region, approved the study protocol on March 9, 2005. Participation in the study is voluntary. Written consent must be obtained from all participating informal caregivers (see the section *Informed consent procedure*). Informal caregivers must explicitly be informed about the fact that they can withdraw their consent any time, without any specific reason, and with no negative consequences with regard to healthcare treatment now or in the future. Patient-caregiver dyads who withdraw from the study will continue to receive treatment from the professional they are assigned to. If a patient is institutionalized, or has died, the caregiver will no longer be invited to follow-up appointments.

Professionals from the health services allocated to the control group will not receive the SCPD training during the trial. However, they will be offered such training after the trial. This means that they can enter the SCPD, but with a 12-month delay.

Names of patient-caregiver dyads and other confidential information will be treated with medical confidentiality, and data are always separated from the names of the patient-caregiver dyads. Each participant is identified in the database by a number and an identity code. These codes are available only to the investigators and the research assistant.

The target groups are people with dementia, their informal caregivers, caregiver organizations, Alzheimer societies, professional healthcare workers, researchers of dementia care, and policy makers. The results of and information about the SCPD will be disseminated in publications and presentations at scientific and professional conferences and directly to family caregivers in Alzheimer cafes. The health services will also spread the results through their regional contacts.

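### Caregiver QALYs are counted only until the patient's admission, and EQ-5D and RUD collection appears to stop there too, so cost per QALY does not compare the arms over a common 12 months

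*Protocol article*

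**What the plan says.** All references are to the Protocol article.

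- **QALY method and span.** Economic evaluation: "We will use QALYs computed with the trapezium rule for a cost-utility analysis of the two treatment groups". The utilities come from the EQ-5D, which Table 1 assigns to the informal caregiver, so these are caregiver QALYs. Their span is limited: "the quality of the caregiver's life will be researched until the time of the patient's institutionalization, with a maximum of 12 months".
- **EQ-5D schedule.** Table 1 lists the EQ-5D at T0 and T4 only.
- **Cost data.** Economic evaluation: "The RUD instrument will be completed by the informal caregiver every 3 months from baseline to follow-up at 12 months". Table 1 agrees, with residence and healthcare use at T0 to T4. The same paragraph then says: "The time to institutionalization is the final event".
- **Contact after admission.** Ethical principles: "If a patient is institutionalized, or has died, the caregiver will no longer be invited to follow-up appointments".
- **Purpose.** The comparison is made "versus usual care for the caregivers, from a societal perspective". Of the primary outcome, admission, the Abstract says: "This measure is the most important variable for estimating cost differences between the intervention group and the control group".

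**The concern.** The QALYs belong to the caregiver, but the clock is stopped by an event that happens to the patient. A caregiver whose patient is admitted at month 6 is still alive in months 7 to 12. Ending the count at admission is arithmetically the same as giving that caregiver a utility of zero from then on. The QALY difference then partly restates the difference in time at home, and cost per QALY overlaps with the other planned ratio, cost per unit of time to institutionalization.

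Two further problems follow from the data rules. With EQ-5D at T0 and T4 only and no invitation after admission, the area under the utility curve cannot be computed for admitted dyads by the stated method. On the cost side, the person who completes the RUD is no longer invited once the most expensive resource starts to be used, although the RUD schedule runs to month 12. The costs that are hypothesised to be saved are those most likely to go uncollected.

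At stake is the cost-per-QALY result. The Abstract makes the start of national implementation depend on the SCPD proving efficient.

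**Working it through.** **Inputs from the Protocol article (Power calculations).** Admission within 12 months: 28% control, 14% intervention; 80% power; two-sided 0.05; 132 dyads per group, inflated by 1.15 to 152.

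**Assumptions (not in the document).** Caregiver utility is constant, equal in both arms and unchanged by admission; values from 0.6 to 0.9 are tried. Admissions follow a constant hazard, or fall on average at month 3, 6 or 9.

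**1. The plan's own figure.** n = [1.96·√(2·0.21·0.79) + 0.8416·√(0.28·0.72 + 0.14·0.86)]² / 0.14² = (1.129 + 0.478)² / 0.0196 ≈ 131.7, so 132. Then 132 × 1.15 = 151.8, so 152. Both are reproduced. The plan states no numerical figure for the economic evaluation.

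**2. Time at home within 12 months.** With mean admission at fraction m of the year, it is 1 − p(1 − m). Under a constant hazard, it is p/L with L = −ln(1 − p): 0.28/0.3285 = 0.852 and 0.14/0.1508 = 0.928.

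**3. QALY difference with identical caregiver health.** Truncated rule: utility × difference in time at home. Fixed 12 months: utility × (1 − 1) = 0.

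| Admission timing | Home, control (y) | Home, intervention (y) | Difference (y; days) | QALY at 0.6 | at 0.8 | at 0.9 |
|---|---|---|---|---|---|---|
| Constant hazard | 0.852 | 0.928 | 0.076; 28 | 0.046 | 0.061 | 0.068 |
| Mean month 3 | 0.790 | 0.895 | 0.105; 38 | 0.063 | 0.084 | 0.095 |
| Mean month 6 | 0.860 | 0.930 | 0.070; 26 | 0.042 | 0.056 | 0.063 |
| Mean month 9 | 0.930 | 0.965 | 0.035; 13 | 0.021 | 0.028 | 0.032 |

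For mean month 6 and utility 0.70 to 0.85: 0.14 × 0.5 × 0.70 = 0.049 and 0.14 × 0.5 × 0.85 = 0.060.

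**4. What the truncation could hide (constant hazard, utility 0.8).** The intervention could lower caregiver utility throughout by 0.8 × (1 − 0.852/0.928) ≈ 0.065 and still tie. If utility rose by 0.10 after admission, the 12-month difference would be −0.10 × 0.076 = −0.008, while the truncated rule would still show +0.061.

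**5. Whether the trapezium can be computed.** It needs at least two utilities. A dyad admitted before T4 and not invited again has only T0. Per 152 dyads that is up to 152 × 0.28 ≈ 43 control and 152 × 0.14 ≈ 21 intervention. It is an upper figure because an admission after month 9 may come to light only at T4 itself.

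**6. Institutional days after admission, per dyad randomised.** Mean month 6: 0.28 × 0.5 × 365 = 51.1 v 0.14 × 0.5 × 365 = 25.6, a difference of 25.6. All of these go uncollected only if the RUD that detects the admission records none of the stay. If admissions fall evenly within the 3-monthly intervals, about 365/8 = 45.6 days precede that RUD and may be recorded. That leaves 182.5 − 45.6 = 136.9 days per admission: 0.28 × 136.9 = 38.3 v 0.14 × 136.9 = 19.2, a difference of about 19. If the RUD does continue to month 12, the loss is nil.

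**The case against.** **The QALY gain is conditional.** If admitted dyads have one EQ-5D value, their QALY may be missing rather than truncated. A complete-case analysis with equal utilities would then show no spurious gain. This stands: the figures in step 3 apply only if a truncated QALY is actually computed. The alternative is no better, because missingness would be driven by the primary outcome and would be about twice as frequent in the control arm.

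**Stopping both costs and effects at admission might be called consistent.** It is not a like-for-like comparison, because the arms are then observed for different lengths of time and the arm with later admission accrues home-care costs for longer.

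**A reader might infer that nursing-home costs are never observed.** The document does not support that. Admission is assessed every 3 months, the detecting RUD may record part of the stay, and both Table 1 and the Economic evaluation schedule the RUD to month 12. The rule in Ethical principles concerns appointments, while questionnaires are returned by post, so its reach is unclear. Later days could also be priced from the admission date. What remains is an unreconciled conflict and no stated pricing rule.

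**A reader might infer that the bootstrap ignores clustering.** The text names no resampling unit, and the Economic evaluation says its effect analysis follows the cluster-randomised design. The unit can properly be left to a fuller plan.

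**A reader might infer that the trial's main conclusion is at risk, or that cost per QALY is biased in a known direction.** Neither follows. The primary analysis of admission and time to admission does not use these rules. Policy implications ties wider implementation to effectiveness, so the implementation decision does not rest on this ratio alone. The two distortions oppose each other.

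**Conclusion.** The rule is wrong as written for the cost-utility analysis. Followed literally, it either gives a living caregiver no QALYs after the patient's admission or leaves up to about 28% v 14% of dyads with a QALY that the stated method cannot produce.

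If truncated QALYs are computed, caregivers in identical health still show a gain for the arm with later admissions: about 0.05 to 0.06 QALY at 28% v 14% with mean admission at month 6 and utility 0.70 to 0.85, and about 0.02 to 0.095 over the wider range tried. The size rests on assumed timing and utility. The direction does not, provided that utilities are positive and one arm spends longer at home.

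On costs, the statements on RUD collection after admission contradict each other. With mean admission at month 6, at most about 51 v 26 institutional days per dyad go uncollected, and fewer if the detecting RUD records part of the stay. This omission works against SCPD, whereas the QALY truncation favours it. They act on different parts of the ratio, and nothing in the document makes them cancel.

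The effect is mainly on cost per QALY. The cost gap also enters the numerator of the ratio based on time to institutionalization, but the QALY rule does not touch that ratio's denominator.

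**What to change.** 1. Delete the rule that ends the caregiver's quality-of-life count at institutionalization. Use a fixed 12-month horizon for costs and QALYs in every dyad, whether or not the patient is admitted.
2. Reconcile Economic evaluation and Table 1 with Ethical principles, so that the remaining RUD questionnaires and the T4 EQ-5D are still sought by post after admission.
3. Where these data were not collected, price the days from the admission date to month 12 at the Dutch guideline price, impute the missing utilities, and state both rules in advance.

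The cost is modest. The contact rule sits under Ethical principles in an approved, ongoing trial, so a small protocol or ethics amendment may be needed. Extra questionnaires would go to about one dyad in five: (28% + 14%)/2 = 21%, or about 43 + 21 = 64 of 304 dyads at 152 per group. Steps 1 and 3 need no new contact with caregivers and can be adopted even if the amendment is not feasible, at the price of relying on imputed utilities for admitted dyads.
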